#### Physical activity and cardiorespiratory fitness

We will use two types of physical activity measurement methods: self-report and objective. The self-administered, long version of the International Physical activity Questionnaire (IPAQ) will be used to assess self-reported physical activity level, as it may provide the most reliable data for the present study [36]. IPAQ is one of the most used and evaluated questionnaires [36]. However, self-report methods may be subject to recall bias and may provide different results compared to objective instruments such as accelerometers [37]. Therefore, we will also use ActiGraph accelerometers, which are most commonly used in research to provide an objective measure of duration, intensity and frequency of physical activity. Physical activity during all waking hours in a 10-day period will be measured every second month with ActiGraph GT3X accelerometers (Pensacola, Florida, USA). The GT3X accelerometer provides sufficient storage capacity for the measurement period, shows high intra- and inter-monitor reliability [38,39] and may capture a wide range of physical activity intensities [40,41]. A period of 10 days provides sufficient information to capture the variation in physical activity [42].

Cardiorespiratory fitness will be assessed by measuring maximum aerobic capacity (VO_2_ max). Subjects will undergo a 6-minute walking test that provides an indirect estimate of oxygen uptake [43] and that has been validated in subjects up to 65 years of age [44]. Performance is estimated by measuring heart rate and walking time at the end of the test, with adjustment for age, gender and BMI. A prerequisite for conducting the test is the ability to walk briskly and to achieve a heart rate of ≥70% of the age-related maximal heart rate.

#### Dietary measurements

The participants will fill in forms with questions covering frequency and estimated level of intake of different foods (such as meat, fish, vegetables, potatoes, rice and cereals fruit, and different snacks), and how the food was prepared (cooked, deep fried, fried), to capture total food intake and habits (breakfast, lunch, dinner, snacks and beverages) during the last three days. Since there are no validated food questionnaires for Arabic foods and food habits, the questionnaires will be developed in collaboration with nutritionists and Arabic-speaking health coaches with knowledge about Arabic food habits and culture. The amount of food will be estimated by the participants by using “*Måltidsmått*” from the pharmacies in Sweden (a picture of *Måltidsmåttet* is presented at http://www.maltidsmattet.se/), which provides a measure of the volume of food. Special attention will be given to food habits during weekends and holidays. The food questions will be analyzed for nutrient content using Dietist XP software. The software contains food tables from the Swedish National Food Administration and includes almost 1600 food items and 50 nutrients [45].

#### Tobacco use

Daily smoking increases the risk of 58 different conditions (including cancer, CVD and pulmonary disorders), which together account for almost 10% of the total disease burden in Sweden [46]. Current smoking status (smoker or non-smoker) will be assessed, together with number of cigarettes per day for smokers. In addition, participants will be asked whether they use snuff or smoke water pipes.

#### Alcohol use

The self-reported version of the Alcohol Use Disorders Identification Test (AUDIT) from the World Health Organization (WHO) [47] will be used to assess alcohol intake habits. A total score of ≥8 will be used as an indicator of hazardous and harmful alcohol use, as well as possible alcohol dependence.

### Physical and mental well being

#### Health-related quality of life

Health-related quality of life will be measured using the EQ-5D questionnaire [48]. All participants (intervention and control groups) will complete the Arabic version of the questionnaire at the start, middle and at the end of the study.

#### Hospital anxiety and depression scale

We will use the Hospital Anxiety and Depression Scale (HADS) [49] to measure the level of anxiety and depression that each participant is experiencing before implementation of the lifestyle intervention. Although HADS was initially developed for hospital patients, it is valid for primary health care patients [50], as is the Arabic version as well [51] that will be used in this study.

### Motivation and behavioral change

#### Stage of change questionnaire

Stage of change is a model developed by Prochaska and colleagues [52]. It identifies five stages that individuals cycle through as they change specific “health-risk” behaviors and the individuals move through a series of stages in their attempts to accept the desired behavior. The stages represent a period of time as well as a set of tasks needed for movement to the next stage. The stage of change questionnaire will be used to identify each participants stage in their change towards healthy lifestyle habits (Table 2) and special care will be provided to treat them accordingly [53]. The scientific evidence for the effect of stage-targeted interventions for individual factors (*e.g.* smoking cessation, fat intake reduction) is strong, but the evidence for complex lifestyle interventions is limited [54].

**Table 2 T2:** Stage of change questionnaire

**Response**	**Stage**
I am currently not very physically active and I do not intend to become more physically active during the next 6 months	Precontemplation
I am currently not very physically active, but I’ve been thinking about increasing my activity level during the next 6 months	Contemplation
I am currently not very physically active, but I am determined to increase my activity level during the next 6 months	Preparation
I am currently physically active, but I’ve only been so for the last 6 months	Action
I am currently physically active and I have been so for longer than 6 months	Maintenance
I was physically active a year ago, but in recent months I have been less active	Relapse
I do not know	

#### Self-determination theory

Self-determination theory (SDT) is a general theory of human motivation that aims to explain individuals’ goal-directed behavior. It explains the extent to which behaviors are autonomous (*i.e.* originate from the self) and the extent to which they are controlled by societal pressure and intrapsychic or interpersonal forces [55]. There is consistent evidence of the value of using SDT to understand physical activity behavior [56]. For the current study, we will use the treatment self-regulation questionnaire (TSRQ), which was designed to assess the different forms of motivation within SDT to determine participants’ motivation to adopt healthy lifestyle habits. The TSRQ has been validated for physical activity and healthy eating habits [57].

### Costs

Direct medical costs, direct non-medical costs and indirect costs will be calculated for both the intervention and control groups. Direct medical costs represent expenditures for medical services and products and are usually paid for by the health systems. These costs include the cost of hospitalization, outpatient care, laboratory tests and medications. Direct non-medical costs include time costs of participation in the exercise program, shopping, food preparation and cooking, and costs of exercise equipment, special foods and transportation. Indirect costs are productivity loss costs due to diseases.

Costs will be further divided into those borne by the program and those incurred by the study participants. Program costs include training costs and costs associated with setting up and performing the intervention. They also include resources required for meetings, staff preparation, meeting time and materials for the participants. Overhead and administrative costs will also be calculated according to recommended methods. Intervention providers (health coaches, nutritionists, physiotherapists, nurses, medical doctors, etc.) will be interviewed to determine the time they spent on each participant and the cost will calculated from their salary chart sheet. For cost calculation, we will use previously developed and validated questionnaires of the Diabetes Prevention Program (DPP) [13]. Each participant will be asked about the specific costs of their transport to and from the health care center, time costs and informal care costs (costs incurred by accompanying persons). Each participant will be asked about their sickness leave in the past two months. Participants will report their general sickness absence in general and also sickness absence due to physical exercise-related injuries. Lost days of productivity will be converted into costs by the human capital method to get the indirect cost.

### Economic evaluation

Cost-effectiveness analysis will be performed from patient, health care and societal perspectives. In the societal perspective, all costs are included irrespective of who is burdened by them, while the health care perspective is only concerned with costs burdening the health care sector. The patient perspective focuses on the costs that the patients have to bear to change their lifestyle habits through the intervention. The societal perspective is generally preferred, although a health care perspective supplies additional (affordability) information and can strengthen conclusions based on the societal perspective. The results will be presented in terms of incremental cost-effectiveness ratios (ICERs), which show the change in costs for an incremental benefit [19]. To determine the cost-effectiveness of the intervention, ICERs will be calculated for all statistically significant outcomes. In cost utility analysis, utility values will be calculated using the EQ-5D questionnaire which provides the health related quality of life as quality adjusted life years (QALY).

We will perform economic evaluation in two different time horizons; short-term (within-trial) and long-term. Within-trial economic evaluation will only focus on the trial cost data and the outcomes. For long-term duration, we will develop a decision analytic model based on the outcome of the trail. This will be done by extrapolating the secondary clinical outcomes (BMI, blood pressure, lipid profile) to predict future disease events such as CVD, diabetes and diabetes-related complications. Each disease event will have a future cost and QALY. Future costs and effects will be discounted by 3% per year, but we intend to perform sensitivity analyses on other rates [58]. We will analyze uncertainty by both one-way and multi-way sensitivity analysis, and also by non-parametric bootstrapping. We will calculate 95% confidence intervals for the ICERs.

We will also calculate the willingness to pay (WTP) to be in the program of the participants by the contingent valuation method. In this method, participants are directly asked what they are willing to pay for a benefit or service [19]. There are many ways to formulate WTP *i.e.* open-ended, closed-ended or biding game type [59]. For the current study, we will use closed-ended questions with predetermined maximum WTP options. The monetary value will represent the annual subscription fee for several commercial gymnasiums in Sweden. Participants will be asked to give reasons for their willingness and unwillingness to pay. The methodology will follow that used in two previously published studies with similar lifestyle interventions [60,61].

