#### Cost-effectiveness analysis

It is assumed that the point estimates for differences in mean cost and QALY between the intervention and control groups will be 1000 SEK and 0.18 QALY, respectively, with differences in the SDs for cost and QALY of 5000 SEK and 0.26 QALY, respectively. The sample size of 260 (130 per group) provides 0.84 power, assuming that the WTP is 1.3 million SEK [64,65].

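### Within-trial ICERs are tied to statistical significance, which selects overstated effects and can leave a planned within-trial ICER, including cost per QALY, unreported

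*Protocol article*

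**What the plan says.** The rule is in the protocol article, Economic evaluation: "To determine the cost-effectiveness of the intervention, ICERs will be calculated for all statistically significant outcomes". The next step described there is a cost-utility analysis: "In cost utility analysis, utility values will be calculated using the EQ-5D questionnaire which provides the health related quality of life". That sentence neither repeats the significance condition nor lifts it.

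The same section plans two time horizons. The short-term evaluation uses only trial costs and outcomes. The long-term evaluation is a decision model built by "extrapolating the secondary clinical outcomes (BMI, blood pressure, lipid profile) to predict future disease events", and "Each disease event will have a future cost and QALY". No significance condition is attached to the model.

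On uncertainty, the section says "We will analyze uncertainty by both one-way and multi-way sensitivity analysis, and also by non-parametric bootstrapping" and "We will calculate 95% confidence intervals for the ICERs".

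The power statement under Cost-effectiveness analysis treats cost and QALY jointly. It assumes that the "point estimates for differences in mean cost and QALY between the intervention and control groups will be 1000 SEK and 0.18 QALY", with SDs of 5000 SEK and 0.26 QALY and 130 per group, and gives a power of 0.84, "assuming that the WTP is 1.3 million SEK".

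**The concern.** Cost-effectiveness is a joint statement about a cost difference and an effect difference. An effect that misses significance still carries information for that statement, and its imprecision belongs in the interval around the result. If an ICER is produced only when the effect passes a test, two things follow.

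- **Selection.** Estimates that pass the test are, on average, larger than the truth unless power is close to 1. The effect is the denominator of the ICER, so with a positive cost difference the reported ratio is too low and looks too favourable.
- **Gaps.** When the effect does not pass, the within-trial ICER for that outcome is not produced, even though it belonged to the plan.

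The rule also fits poorly with the rest of the article. Bootstrapping, and a power basis combining cost, QALY and WTP, both work without significance on any single outcome. Cost-effectiveness is the fourth aim of the study, and the Abstract offers the results to policy makers. A result that is selected by p-value is a poor basis for that.

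**Working it through.** **Inputs**

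- Fasting glucose: difference 0.22 mmol/L, SD 0.6, stated power 0.86 (Sample size and power calculation).
- QALY: difference 0.18, SD 0.26; cost: difference 1000 SEK, SD 5000 SEK; WTP 1.3 million SEK; stated power 0.84 (Cost-effectiveness analysis). The article's wording on the SDs is unclear; they are read here as per-person SDs.
- 130 completers per group (Eligibility criteria).
- Significance level: not stated for the power calculations. Two-sided 0.05 is assumed, in line with the planned 95% intervals.
- QALY gains below 0.18 are assumptions, used to show a range.

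**The plan's own figures first**

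- Glucose: SE = 0.6 × √(2/130) = 0.0744, and 0.22/0.0744 = 2.96. Power = Φ(2.96 − 1.96) = 0.840, against 0.86 stated. This is close enough to work with.
- Net benefit: difference = 1,300,000 × 0.18 − 1000 = 233,000 SEK. SD = √((1,300,000 × 0.26)² + 5000²) ≈ 338,000 SEK with uncorrelated cost and QALY. Power at 130 per group is 0.9998, not 0.84, and it stays at 0.9998 to 0.9999 for any correlation from −1 to 1. The stated 0.84 is not reproduced. That is a separate matter and does not decide this point.

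**Effect of the gate**

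Let λ = true difference / SE and c = 1.96.

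- Chance that the ICER is missing = 1 − [Φ(λ − c) + Φ(−λ − c)].
- Mean of the positive significant estimates relative to the truth = 1 + φ(c − λ) / [λ Φ(λ − c)].

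*Fasting glucose.* The smallest significant difference is 1.96 × 0.0744 = 0.146 mmol/L. With a true difference of 0.22:

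- missing: 1 − 0.840 = 0.16;
- overstatement: 1 + 0.243/(2.96 × 0.840) = 1.10.

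As an illustration, hold the cost difference at the article's 1000 SEK. The true ratio is 1000/0.22 = 4545 SEK per mmol/L. At the mean selected effect of 0.22 × 1.10 = 0.242 it is 1000/0.242 = 4132 SEK, about 9% too low.

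*QALY.* SE = 0.26 × √(2/130) = 0.0322. The smallest significant difference is 1.96 × 0.0322 = 0.063 QALY.

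| True QALY difference | Source | Within-trial cost per QALY missing | Mean overstatement when positive and significant |
|---|---|---|---|
| 0.18 | article | 0.01% | 1.00 |
| 0.10 | assumed | 13% | 1.08 |
| 0.05 | assumed | 66% | 1.69 |
| 0.03 | assumed | 85% | 2.67 |

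**Are smaller gains plausible?** Follow-up is 6 months, so full health throughout is worth 0.5 QALY. A gain of 0.18 needs a mean utility gap of 0.18/0.5 = 0.36 over the whole period. With equal baselines, EQ-5D at 0, 3 and 6 months, the trapezoid rule and the same gap g at both follow-ups, the gain is (0.125 + 0.25) × g. So g = 0.18/0.375 = 0.48. A true gain well below 0.18 therefore has to be considered.

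**The case against.** The strongest objection is that the article never says ICERs are limited to significant outcomes. The cost-utility analysis has its own sentence without the condition, and the power statement shows that a QALY analysis is intended. That is fair as far as it goes. But the significance wording does nothing in the sentence unless it restricts, and nothing exempts QALYs. Restriction remains the natural reading, and the ambiguity itself needs settling.

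A reader might infer more: that a non-significant QALY difference would leave the study with no cost per QALY at all. The documents do not support this. The long-term model derives costs and QALYs from BMI, blood pressure and lipids with no significance condition. The gap concerns the within-trial result only.

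A reader might also infer that a within-trial cost per QALY will probably be missing. On the article's own 0.18 and 0.26 the gate almost never binds. The high percentages in the table depend on assumed smaller gains.

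It is also true that chance could hand an ICER to an outcome with no real effect. The documents fix neither the number of outcomes eligible for an ICER nor their correlation, so no figure is put on this.

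One could defend the gate as a guard against unstable ratios, since it largely excludes effects whose interval includes zero. That motive is sound, but net benefit avoids the instability without selecting on the result.

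Finally, at a cost difference of 1000 SEK even a gain of 0.03 gives 1000/0.03 = 33,333 SEK per QALY, far below the stated WTP. Overstatement alone would then not reverse a decision based on point estimates. This stands, but only for that assumed cost. It does not excuse a biased or missing estimate.

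**Conclusion.** The point holds for the within-trial evaluation. As worded, the ICERs there depend on significance, QALYs included, and this both inflates reported effects and can suppress a planned result. On the article's glucose assumptions the ICER is lost in about 16% of trials and the effect is about 10% too large when it is kept. For QALYs the loss runs from practically none at a gain of 0.18 to 85% at 0.03, with overstatement from 1.00 to 2.67 times.

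These sizes rest on two-sided 0.05, 130 per group, a normal approximation without covariate adjustment, SD 0.26 kept at every QALY gain, and assumed gains below 0.18. The long-term model, the randomization and the primary glucose comparison are not affected.

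**What to change.** - Delete the significance condition from the Economic evaluation section, and say that the QALY analysis is unconditional.
- Report the within-trial incremental cost, incremental QALY and incremental fasting glucose, with cost per QALY and cost per mmol/L, whatever the p-value.
- Use the bootstrap already planned to give incremental net benefit with a 95% interval at the stated WTP. This is the scale implied by the power statement, and it stays interpretable when the effect interval includes zero, where an interval for the ratio may not.

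The cost is a change of wording and minor analysis work, with no extra participants or measurements. The downside is that some intervals may be wide and less favourable. The change should be made before results are known, because lifting the condition afterwards would look driven by the data.

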**Methods/design:**

In this randomized controlled trial, 308 participants (born in Iraq, living in Malmö, Sweden and at high risk of type 2 diabetes) will be allocated to either a culturally adapted intervention or a control group. The intervention will consist of 10 group counseling sessions focusing on diet, physical activity and behavioral change over 6 months, and the offer of exercise sessions. Cultural adaptation includes gender-specific exercise sessions, and counseling by a health coach community member. The control group will receive the information about healthy lifestyle habits provided by the primary health care center. The primary outcome is change in fasting glucose level. Secondary outcomes are changes in body mass index, insulin sensitivity, physical activity, food habits and health-related quality of life. Measurements will be taken at baseline, after 3 and 6 months. Data will be analyzed by the intention-to-treat approach. The cost-effectiveness during the trial period and over the longer term will be assessed by simulation modeling from patient, health care and societal perspectives.

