### Follow up and evaluation of data

The intervention and control groups will be followed up every 3 months for BMI, fasting glucose, HbA1c, blood pressure, diet registration, physical activity and fitness, and with questionnaires. The final evaluation conducted after 6 months will also include an OGTT.

We will study whether the intervention has a significant effect on fasting glucose levels and whether this effect is depending on ISI, DIo or family history of diabetes. We will also study factors that may predict these changes, including intensity and amount of physical activity (measured with ActiGraph accelerometers and questionnaires) and behavioral factors such as stage of change and motivation level (measured with questions originating from self-determination theory).

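### The long-term cost-effectiveness model names BMI, blood pressure and lipids as the trial effects that predict future diabetes, but no glycaemic measure, although fasting glucose is the primary outcome

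*Protocol article*

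**What the plan says.** The abstract fixes the outcome hierarchy: "The primary outcome is change in fasting glucose level", and "Secondary outcomes are changes in body mass index, insulin sensitivity, physical activity, food habits and health-related quality of life". Under Aim/purpose, aim 2 asks about the effect on glucose metabolism, measured by fasting glucose. Aim 4 asks for cost-effectiveness over a short and a long horizon.

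The Economic evaluation section treats the two horizons differently. For the trial period: "Within-trial economic evaluation will only focus on the trial cost data and the outcomes". For the longer horizon: "For long-term duration, we will develop a decision analytic model based on the outcome of the trail". The next sentence says how: "This will be done by extrapolating the secondary clinical outcomes (BMI, blood pressure, lipid profile) to predict future disease events such as CVD, diabetes", and it goes on to name diabetes-related complications. The long-term result is then built from those events: "Each disease event will have a future cost and QALY".

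Glycaemic data exist at follow-up. Under Follow up and evaluation of data, both arms are "followed up every 3 months for BMI, fasting glucose, HbA1c, blood pressure, diet registration", among other measures. Table 1 schedules fasting plasma glucose, HbA1c and the OGTT at baseline, 3 months and 6 months.

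**The concern.** The trial's rationale is diabetes prevention, and its power calculation is on fasting glucose. The long-term model is where the health and cost consequences of prevented diabetes are counted. The article nevertheless specifies that future diabetes is predicted from three outcomes that it calls secondary, and the primary outcome is not among them.

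The protocol's own reasoning makes this more than a formality. Inclusion criterion A defines high diabetes risk by fasting and 2-hour glucose. The Background cites benefits of exercise for beta-cell function in people at high risk, and the Exercise sessions section cites benefits of training for glucose metabolism in people with IGT. A glucose effect that is not fully explained by weight, blood pressure or lipids is therefore something the trial has reason to expect.

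At stake is the agreement between the long-term result and the primary result. If glucose improves by more than the named inputs reflect, the model understates the diabetes prevented. If BMI falls and glucose does not, the model may credit prevention that the primary outcome does not support.

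**Working it through.** The article attaches no numerical claim to the model inputs, so there is no figure to reproduce. The check is a reading of the sections side by side, followed by a simple decomposition.

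**Step 1: what is named as an input.**

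| Measure | Role in the abstract | Collected at follow-up | Named as long-term model input |
|---|---|---|---|
| Fasting glucose | Primary | Yes (Table 1; Follow up and evaluation of data) | No |
| HbA1c | Not listed | Yes (both places) | No |
| 2-hour glucose (OGTT) | Not listed | Yes, at 6 months in both places | No |
| BMI | Secondary | Yes | Yes |
| Blood pressure | Not listed | Yes (Follow up and evaluation of data) | Yes |
| Lipid profile | Not listed | Yes (Table 1) | Yes |

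The absence of a glycaemic input is therefore not forced by missing data.

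**Step 2: is the list open or closed?** The sentence uses open wording for the disease events and none for the inputs in the bracket. It also restricts them to secondary outcomes. No other section adds a glycaemic input. The natural reading is a stated choice of inputs. The preceding general sentence, which bases the model on the trial outcome, leaves some room for a wider reading.

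**Step 3: what reaches the long-term result.** By the article's own chain, the named inputs predict events, and events carry costs and QALYs. Write the between-arm glucose effect as

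total effect = part carried by BMI, blood pressure and lipids + remaining part.

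As written, only the first part has a route into predicted diabetes. Let c be the share carried by the named inputs. The part without a route is (1 − c) × total effect.

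**Step 4: range on the glucose scale.** The planned difference is 0.22 mmol/L with SD 0.6 (Sample size and power calculation), that is 0.22 / 0.6 = 0.37 SD. The article gives no value for c, so it is an assumption, shown over its range:

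- c = 1: (1 − 1) × 0.22 = 0 mmol/L unrepresented.
- c = 0.5: (1 − 0.5) × 0.22 = 0.11 mmol/L unrepresented.
- c = 0: (1 − 0) × 0.22 = 0.22 mmol/L unrepresented.

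**Step 5: conversion to cases, QALYs or costs.** This needs a risk equation linking the inputs to diabetes incidence. The article gives none, so no figure can be derived.

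**The case against.** The best case for the plan has four parts.

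- **The wording leaves room.** The model is said to rest on the trial outcome, and the bracket can be read as listing which of the secondary outcomes are used, without excluding the primary one. A reader might infer that glucose is expressly shut out; the article never says so. This softens the finding but does not remove it, because the sentence that explains how the model works names no glycaemic measure.
- **A condensed article leaves model detail elsewhere.** Risk equations, health states and transitions properly belong in a fuller plan, and their absence is no finding. Here, however, the inputs themselves are named, and a fuller plan would have to depart from or extend that sentence to bring glucose in.
- **BMI would carry part of the effect.** The intervention combines diet and exercise and has a goal of at least 5% weight reduction. A reader might infer that a glucose effect could not enter the model at all, or that no diabetes would be averted on paper. That holds only if BMI, blood pressure and lipids all stay unchanged, which the documents give no reason to expect.
- **Other results can show a glucose effect.** The within-trial evaluation uses the trial outcomes, and "ICERs will be calculated for all statistically significant outcomes", which would include fasting glucose if it is significant. A reader might infer that an effective program would be declared not cost-effective overall. The article does not support that, because only one of two horizons is affected.

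The abstract's shorter list of secondary outcomes is weak evidence of contradiction, since an abstract abbreviates.

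**Conclusion.** The point stands in a limited form. Followed as written, the long-term model gives no route to the part of a glucose effect that is independent of BMI, blood pressure and lipids, so the long-term part of aim 4 could disagree with the primary result in either direction. On the glucose scale the unrepresented part is between 0 and 0.22 mmol/L of the planned effect, depending on an unknown share. Its size in QALYs or costs cannot be stated.

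The conclusion rests on reading the bracketed inputs as a closed list, which the grammar favors but does not prove. Randomization, sample size, the primary analysis, data collection and the within-trial evaluation are untouched. The matter should be settled before the model is built.

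**What to change.** Amend the Economic evaluation section so that the between-arm difference in fasting glucose, with HbA1c or 2-hour glucose, enters the diabetes-incidence part of the long-term model. It should enter alongside BMI and the other named risk factors and not replace them, since the Background itself treats obesity as a diabetes risk factor. Add a sensitivity analysis with the currently named inputs alone, so that readers can see how much of the long-term result depends on the glycaemic input. If the sponsor prefers to leave glucose out, the section should say so and give the reason.

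The cost is a sentence or two of specification and a little more modelling work. No new measurement is needed.

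A separate clerical point can be corrected at the same time. Blood pressure is a named model input but has no row in Table 1, although Biomedical measurement gives the method and Follow up and evaluation of data gives the 3-monthly schedule. Adding the row would align the three places; it has no bearing on whether glucose enters the model.
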